## Assignment of interventions: allocation

### Sequence generation {16a}

The randomisation sequence is generated before the start of the study with 1:1 allocation using random block sizes of 2 and 4. With each successive recruitment, patients will be assigned to the treatment arm consecutively based on their sequence on the generated list. The patient will receive a Trial Identification Number based on their position of the sequence.

To begin the trial, Study personnel will collect assigned trial medication from the organization’s pharmacy and bring along to the home visit. The material packs prepared for the trial will then be marked in the order of the randomised allocation; this allows for the investigators to more easily and more quickly identify the pack to pick up and deliver to the patient.

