### Concealment mechanism {16b}

Not applicable.

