### Implementation {16c}

The study team’s research executive will generate the randomisation sequence and number the prepared medication packs accordingly. These packs will be placed in secure storage within the organization’s pharmacy. The investigators, when visiting the patient to collect informed consent, will subsequently collect the packs and deliver them to the family.

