#### The Memorial Delirium Assessment Scale

MDAS is a ten-item, four-point clinician-rated scale designed to quantify the severity of delirium in medically ill patients [13]. It has very good psychometric properties, with high reliability (*r* = .91) and good discriminant and concurrent validity. Though the scale was intended to assess patients based on all ten items, it was suggested that items in MDAS can be pro-rated in the event the patient is not able to communicate (Lawlor, et al., 2000). To conduct assessments as well as to ensure patient’s safety, the study team physician will make regular home visits to assess the patient at the time of the first dose, and then at 24 h, 48 h, and 72 h after the first dose.

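### Allocation concealment is wrongly declared not applicable; as written, the research team that takes consent could often predict the next arm

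*Protocol article*

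**What the plan says.** All references are to the protocol article.

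- **Sequence generation {16a}:** "The randomisation sequence is generated before the start of the study with 1:1 allocation using random block sizes of 2 and 4". There is one list, and "patients will be assigned to the treatment arm consecutively based on their sequence on the generated list". On the packs: "The material packs prepared for the trial will then be marked in the order of the randomised allocation", with the stated purpose that "this allows for the investigators to more easily and more quickly identify the pack to pick up and deliver to the patient". To begin the trial, "Study personnel will collect assigned trial medication" from the pharmacy and take it to the home visit.
- **Concealment mechanism {16b}:** the whole entry is "Not applicable".
- **Implementation {16c}:** the study team's research executive generates the list and numbers the packs, which are kept in secure pharmacy storage. Then: "The investigators, when visiting the patient to collect informed consent, will subsequently collect the packs and deliver them to the family".
- **Intervention description {11a}:** randomisation comes after consent. Haloperidol is a solution given by dropper; olanzapine is an oro-dispersible tablet.
- **Who will be blinded {17a}:** nobody, including the researchers.
- **Who will take informed consent? {26a}:** one site; the proxy is approached by a study team member who gives the patient no direct care.
- **Recruitment {15}:** hospice clinical staff identify patients, confirm delirium and refer them to the research team.
- **The Memorial Delirium Assessment Scale:** the study physician will "assess the patient at the time of the first dose" and at three later times.

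**The concern.** Blinding governs what is known after assignment; concealment governs what is known before it. The Discussion's reasons for not blinding have no bearing on concealment. Because the article answers the item, and answers it wrongly, this is not a detail left to a fuller document.

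The surrounding text describes a procedure in which the team seeking consent has the means to anticipate the arm. It knows past assignments, the blocks are short, and its members handle packs marked in list order whose contents differ in form. Entry also rests on judgement, chiefly an estimated prognosis of 3 days or less (Eligibility criteria {10}). A team that expects a particular arm can, without intending to, be quicker or slower to approach a proxy, or present the study differently.

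The result would be selection bias. Adjustment for measured baseline severity can remove part of it, but selection on unmeasured prognosis cannot be reliably corrected. Outcome rating is unblinded too, so comparability of the arms at entry carries much of the weight of the comparison.

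**Working it through.** The article gives no predictability figure, so there is none to reproduce. The check has two parts.

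**1. How predictable is the next arm from the block structure alone?**

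Inputs: 1:1 allocation, random blocks of 2 and 4, one consecutive list (Sequence generation {16a}); 80 patients (Sample size {14}). Assumptions: the observer knows every past assignment in order and guesses whichever arm is behind, tossing a coin when the arms are level. The mix of block sizes is not stated; equal probability is assumed and the extremes are shown.

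*Expected correct guesses per block*
- Block of 2: 0.5 + 1 = 1.5.
- Block of 4, by position: 1/2; 2/3; (2/3 × 1/2) + (1/3 × 1) = 2/3; 1. Sum = 2.833.

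*Share correct*
- Equal mix: (1.5 + 2.833) / (2 + 4) = 4.333/6 = 72.2%.
- All blocks of 2: 1.5/2 = 75%.
- All blocks of 4: 2.833/4 = 70.8%.

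*Share known with certainty, when block boundaries are not known*

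An excess of two in one arm proves that a block of 4 is under way and fixes its last two assignments. A block of 4 opens with two of the same arm with probability 1/3, so it yields 2 × 1/3 = 0.667 certain assignments.
- Equal mix: 0.667/6 = 11.1%.
- All blocks of 2: 0%.
- All blocks of 4: 0.667/4 = 16.7%.

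Simulating 10,000 lists of 80 with an equal mix gave 72.1% correct and about 11% certain, in agreement. Over 80 patients, 72.2% is about 58 correct guesses, against 40 by chance.

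*Would larger blocks help?*

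For a block of size 2m the expected number correct is m + (4^m / C(2m, m) − 1)/2. This returns 1.5 and 2.833 for m = 1 and 2, and gives 4.1 for m = 3 and 5.329 for m = 4. Blocks of 4, 6 and 8, equally likely: (2.833 + 4.1 + 5.329)/18 = 12.262/18 = 68.1%. The gain over 72.2% is about 4 percentage points.

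**2. Who could know the arm, and when?**

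| Section | Order implied |
|---|---|
| Intervention description {11a} | Consent, then randomisation |
| Sequence generation {16a} | Assigned medication collected from the pharmacy, then taken to the home visit |
| Implementation {16c} | Visit for consent, with packs collected subsequently; can be read as after consent |

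If the first or third row governs, the pack need not be seen before consent. If the second governs, the drug is already assigned and in the team's hands at the visit where consent is sought. No section describes the outside of the pack, so the text does not settle whether handling it reveals the arm. If the contents can be seen, the arm is known every time; if not, the block-structure figures apply.

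**The case against.** Several points on the other side are fair.

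- **Safeguards exist.** Packs are in secure pharmacy storage, the person seeking consent gives no direct care, and two sections can be read as placing assignment after consent. This makes advance sight of the pack a possibility, not an established fact. It does not justify the concealment entry, and Sequence generation {16a} still points the other way.
- **Referring staff.** A reader might infer that everyone involved in recruitment can foresee the arm. The article does not say that referring clinical staff see the list or packs, and they work in five teams (Study setting {9}). Suppose patients fall at random among the five teams and a referrer knows only their own team's past assignments. Guessing the arm that is behind in that team is then right about 52% of the time in simulation. Talk between teams or a better strategy would raise this. The 72% therefore belongs to the research team.
- **Complete foreknowledge.** A reader might infer 100% predictability. That requires seeing the contents. Marking packs in order does not reveal them, and sequential numbering is a normal part of sound concealment.
- **Baseline scores.** A reader might infer that baseline MDAS is rated with the arm already known. The article puts the rating at the first dose but does not say whether it precedes opening the pack. That is a question of step order and rater knowledge, separate from concealment before enrolment, though the same fix settles it.
- **List holder.** The research executive is given no consent duties, so separation of list from recruiters may already be partly in place. The article does not state that the list is kept from the investigators.

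**Conclusion.** The concealment entry is a misstatement and should be corrected before recruitment. Followed as written, the plan lets a research team member who knows past assignments predict the next arm about 72% of the time (71% to 75% across block mixes) and be certain for about 11% (0% to 17%). Both figures assume full knowledge of past assignments in order; the point values also assume blocks of 2 and 4 are equally likely. They measure predictability, not the size of any bias in the treatment effect, which the document gives no means to estimate.

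The exposure is mainly at the research team's approach and consent step. The sections on when the assigned drug is collected conflict and must be reconciled.

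**What to change.** 1. Replace the concealment entry with a mechanism. Keep the list from the investigators who take consent. Use identical, opaque, sealed, sequentially numbered packs, or have the pharmacy release each pack on request.
2. State one order of steps and use it in Intervention description {11a}, Sequence generation {16a} and Implementation {16c}: consent signed, baseline MDAS and RASS recorded with a time, then the next pack assigned and opened.
3. Do not disclose block sizes to those who recruit. Larger varying blocks are an optional, minor addition: 4, 6 and 8 would still leave about 68% predictable from past assignments, with slightly more chance of imbalance at the end of the trial. Sealed allocation after consent and baseline is the substantive change.

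The cost is opaque packaging and one order-of-steps line on the case report form. Dosing, eligibility and sample size are unaffected, and the Trial status section shows recruitment had not begun.

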### Concealment mechanism {16b}

Not applicable.

### Implementation {16c}

The study team’s research executive will generate the randomisation sequence and number the prepared medication packs accordingly. These packs will be placed in secure storage within the organization’s pharmacy. The investigators, when visiting the patient to collect informed consent, will subsequently collect the packs and deliver them to the family.

## Assignment of interventions: blinding

### Who will be blinded {17a}

This study was designed as an open-label study and thus there was no blinding between trial participants, care providers or the researchers.

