### Relevant concomitant care permitted or prohibited during the trial {11d}

There are no limitations on other medications, herbs, vitamins, and mineral supplements other than study agents while participating in the study. Additionally, if there were any assistance required after-hours (related to the trial or not), the caregivers will have access to the emergency helpline. The study team will also be notified to render assistance if needed. All medications (prescription and over the counter), vitamin and mineral supplements, and/or herbs taken by the participant will be documented and used to control for confounding factors if needed.

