### Data management {19}

Each trial will have an associated case report form, which will be reviewed by the visiting investigator after each visit to ensure the accuracy of recorded data.

Data will initially be recorded on hardcopies of the case report forms by both the clinician and caregiver before they are transcribed to a Microsoft Excel file. The file is web-based and access-secured; only the investigators are able to access the file via their hospice organizational account. For electronic data, they will be stored in an encrypted and password-protected excel file. At the completion of data collection and initiation of analysis, participant identifiers will be removed from the file. The de-identified file will remain while the file with participant identifiers will be destroyed

For hardcopy data, they will be stored in designated locked cabinet(s) or room(s) that are accessible to authorized study personnel only. Only the patient’s Trial Identification Number will be used to identify the hardcopy.

Records for all participants, including case report forms, all source documentation (containing evidence to study eligibility, history and physical findings, laboratory data, results of consultations, etc.) as well as Institutional Review Board (IRB) records and other regulatory documentation should be retained by the PI in a secure storage facility. The records should be accessible for inspection and copying by authorised authorities.

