## Discussion

To compare the efficacy of two pharmacological treatments of terminal delirium in dying patients on hospice care, a prospective, randomised, open-label trial will be conducted at home setting. The two groups of patients will be receiving OT haloperidol and olanzapine respectively.

Findings from this study will contribute to scarce evidence of anti-psychotics/ neuroleptics use in the treatment of terminal delirium for patients receiving home hospice care. It would inform future practice on appropriate medication to treat delirium during the dying phase. With optimised care, the end-of-life experience of patients and their caregivers will be improved.

Some facts were discussed during the study design. First, a blinded design will not be possible or necessary. Due to limited clinical evidence of pharmacological treatment of terminal delirium in the home environment, the additional blinding procedures are hazardous and not providing any added value. Second, proxy consent has been chosen instead of advance consent. To approach patients before the onset of terminal delirium is neither feasible nor appropriate considering the potential unnecessary stress caused to the vulnerable group of patients in their terminal phase.

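### Researchers are declared unblinded and no arm-coded analysis file is described, while the analysis set, covariate adjustment and MDAS pro-rating are left contradictory or open

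*Protocol article*

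**What the plan says.** **Blinding.** Section {17a} says "there was no blinding between trial participants, care providers or the researchers". The analyst is not mentioned separately. The Discussion defends the open design on the ground that "the additional blinding procedures are hazardous and not providing any added value", and ties this to the limited evidence on drug treatment of terminal delirium at home.

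**The data file.** Data management {19} says of the electronic file that "only the investigators are able to access the file via their hospice organizational account". The same investigators make the daily home visits (sections {11a} and {11c}). The only change described before analysis is this: "At the completion of data collection and initiation of analysis, participant identifiers will be removed from the file". No coding of the arm is mentioned.

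**The link to the arm.** Under Sequence generation {16a}, "The patient will receive a Trial Identification Number based on their position of the sequence". Under Implementation {16c}, the study team's "research executive will generate the randomisation sequence".

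**Choices left in the text.**
- Day-7 survivors: Provisions for post-trial care {30} takes them out of the main analysis. The last paragraph of {18a} takes them out of a per-protocol analysis. Section {20c} prescribes intention to treat by randomised arm.
- Covariates: under {11d}, other medication is to be documented and "used to control for confounding factors if needed".
- Scoring: the MDAS description in {18a} reports that items may be pro-rated when a patient cannot communicate, but gives no rule for when or how.

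**Aim and test.** Objectives {7} calls the trial non-inferiority. Section {20a} plans a repeated-measures ANOVA.

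**The concern.** In an open-label trial whose ratings are also unmasked, the analysis is one of the few stages where knowledge of the arm can still be withheld. The stated reason for not blinding is about hazard at the bedside. A file coded after the last patient has finished creates no such hazard, so the reason given does not cover the analysis.

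This would matter little if the analysis were fully fixed, but it is not. Whether a patient is alive after day 7 is known only after treatment, and three sections treat such patients in three ways. Adjustment depends on a later judgement of need, and pro-rating depends on a rule not given. If these are settled by people who may know the arm and can see the results, the conclusion that haloperidol is not unacceptably worse could follow from the choice rather than the data.

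**Working it through.** The plan gives no figure on this point, so there is none to reproduce. Table 3 supplies SD 7.64, a 2-point minimal important difference, alpha .05 (sidedness not stated), 32 per arm and 80 to be recruited. Whether those sample-size figures agree with one another is a separate question.

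**1. The analysis set, side by side**

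| Section | Day-7 survivors |
|---|---|
| {30} | out of the main analysis |
| {18a} | out of a per-protocol analysis |
| {20c} | in, under intention to treat |

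The first and third cannot both describe the main analysis. The second agrees with the third only if the per-protocol analysis is a separate, secondary one, and the article does not say so.

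**2. Could the analyst know the arm?** Possibly. The investigators hold the file and visited the patients. The trial number follows the allocation list, so number plus list gives the arm. With random blocks of 2 and 4, the number alone does not. Any recorded dose would also show it (2.5 mg against 5.0 mg). The article does not list the fields of the electronic file or say who runs the analysis.

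**3. Illustration A: what open choices can do**

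From Table 3: n = 32 per arm, SD 7.64, true difference 2. Assumed: 2 points is the margin, and the test is one-sided at 5%. Non-inferiority is declared if d + t·SE < 2, where d is haloperidol minus olanzapine and positive means worse. With the true difference at the margin, one fixed analysis errs in 5% of trials by construction.

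Eight analyses: adjust or not × keep or drop survivors × keep or drop pro-rated scores. There were 4,000 simulated trials per setting, so the Monte Carlo standard error near 5% is √(0.05 × 0.95/4000) = 0.34 points. Survivor and pro-rating status were independent of arm and outcome.

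| Covariate correlation | Survivors | Pro-rated | Best of 8 | Repeat run |
|---|---|---|---|---|
| 0.2 | 10% | 15% | 9.0% | 10.4% |
| 0.4 | 15% | 25% | 12.1% | 12.3% |
| 0.6 | 25% | 35% | 15.5% | 15.1% |

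The fixed analysis gave 4.3–5.4% (repeat: 5.0–5.4%). Choosing by narrowest interval, without regard to arm, gave 5.7–6.1% in the repeat run.

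**4. Illustration B: different assumptions**

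n = 40 per arm (80 at 1:1), correlation 0.5 between visits, one-sided 2.5%, margin and true difference 2, survivors 10–30%. Baseline adjustment stands in for the covariate choice.
- Fixed analysis: 2.3–2.7%
- Better of two populations: 3.2–3.7%
- Adjustment also open: 5.1–5.7%
- Time point also open (16 analyses): 12.1–14.0%

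The last step goes beyond the text, since {20a} makes time-point tests post hoc only.

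**5. What coding can and cannot do**

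For a margin-based test, swapping the labels changes the upper limit from d + t·SE to −d + t·SE, so an analyst who does not know the arms cannot tell which choice favours haloperidol. In B at 20% survivors (6,000 trials), the best of 16 chosen with the arm known erred in 13.9%. Choosing on coded arms the interval whose farther end lay nearest zero erred in 2.2%.

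For the planned ANOVA, the two-arm comparison uses F = (d/SE)², which is the same for d and −d. Codes A and B hide nothing from someone looking for no difference. In the same simulation, with a true difference of 2, one fixed analysis was non-significant in 57.9% of trials, and at least one of the 16 was in 99.0%, coded or not.

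Hand check of 57.9%:
- Variance of the three-visit mean: σ²(1 + 2 × 0.5)/3 = 0.667σ².
- Baseline adjustment removes 0.25σ², leaving 0.417σ².
- SD = 7.64 × √0.417 = 4.93; SE = 4.93 × √(2/40) = 1.10; 2/1.10 = 1.81.
- Non-significance ≈ Φ(1.99 − 1.81) = Φ(0.18) = 0.57, which agrees.

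**The case against.** The strongest case against is that this is detail for an analysis plan. Section {17a} says researchers, not analysts. Coding, covariates and scoring rules commonly sit in a statistical analysis plan, which may exist and is not shown. An open-label trial without analyst masking contradicts nothing. The cure for open choices is to specify them, after which this selection effect vanishes without any masking.

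Much of that stands. That the analyst will be unblinded is an inference, and missing coding alone would be a weak point. What remains is that {17a} is a positive statement naming the researchers, its stated reason does not reach the analysis, and {30}, {18a} and {20c} conflict whatever another document says.

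A reader might also infer more than the article supports:
- *That a coded file would prevent selective analysis.* It would not under the planned ANOVA (step 5), and it could be partly defeated if the analyst had visited patients.
- *That the trial number kept on the electronic data exposes the arm.* Data management {19} says that number is used on the hardcopy. For the electronic file it says only that "participant identifiers will be removed from the file".
- *That those who treated and rated the patients will certainly analyse the file.* Confidentiality {27} places the de-identified file in a folder open to research staff, and no section names the analyst.
- *That pro-rated scores may be dropped.* The text never offers this; Illustration A includes it as an assumption.
- *That coding is free.* Someone must prepare the file and hold the key.

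**Conclusion.** The point holds in limited form. The article declares the researchers unblinded for a reason confined to bedside care, provides no arm-coded analysis file, and leaves one contradictory choice (the analysis set) and two open ones (covariates, pro-rating) that could be settled after results are seen by people who may know the arm. The contradiction is the firmest part. The missing coding is secondary.

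Its size cannot be derived from the documents. The rise from 5% to about 9–16% illustrates what open choices can do under assumed correlations, assumed shares of survivors and pro-rated scores, an assumed 2-point margin and an assumed one-sided interval test. It should not be read as the effect of missing blinding, nor as a departure from a stated 5% non-inferiority error rate: Table 3's alpha has no stated side, and the article calls 2 points a minimal important difference, not a margin. Coding addresses selection by direction under a margin-based test. It leaves the unmasked MDAS and RASS ratings as they are.

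**What to change.** **Main change, before any between-arm comparison is run.**
1. Reconcile {30}, {18a} and {20c} so that one analysis set is primary and the place of day-7 survivors is stated once.
2. Replace the discretionary adjustment in {11d} with a named covariate set, or with none.
3. State when and how MDAS items are pro-rated.
4. Replace the symmetric test in {20a}, for the primary comparison, with a directional one: a confidence limit for haloperidol minus olanzapine set against a margin that the sponsor states and justifies.
5. Date these decisions. If an existing analysis plan already fixes them, cite it and correct the conflicting sections.

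Settling them on the coded file would not be enough, because between-arm results would still be visible.

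**Supplement.** Amend {17a} to say that participants, caregivers, care providers and raters are not blinded, but that the primary efficacy analysis is run with the arm coded. At the de-identification step in {19}, the research executive replaces the arm with A or B, replaces the trial number with a random one, and withholds drug and dose fields. The research executive should not run the analysis, and an analyst who made no home visits is preferable. Toxicity is a secondary outcome whose pattern may reveal the arm, so tabulate it last, after the primary efficacy result is recorded.

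**Cost.** Small but not nil: some redrafting of the article's sections, a few hours of file preparation by existing staff, and custody of the key.
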